**Fig. 2 Fig2:**
[figure not shown]
Training for the Think Healthy Program (THP): intervention versus control arm

### Potential biases

#### Observer blinding

The raters who will assess the competence level of LHWs post training and at 3 months will not be aware of the allocation status of the training methods of the LHWs.

#### Contamination

The THP group supervision for LHWs will be held monthly, in addition to their routine monthly meeting. The LHWs will be advised not to disclose information to their colleagues.

#### Primary outcome – competence of health workers

Primary outcome will be measure of LHW competence in the two groups. Equivalence is defined as a difference of less than 5 points (10 %) in the mean score of the competence measure across the two groups.

##### Outcome measure

The primary outcome of competence will be measured by using the ENhancing Assessment of Common Therapeutic factors (ENACT) scoring system [24]. ENACT is an 18-item scoring system for training and supervision across settings in mental health for global use. ENACT was developed by a process of selecting items through item generation, item relevance, and item utility and piloted in trainings for psychological treatments and the mhGAP. Inter-rater reliability was acceptable for non-specialists [24].

The key areas assessed in this tool are: verbal and non-verbal communication; rapport building; empathy; family involvement; goal setting; exploration of feelings; social support; functioning; life events; coping; mental health problems; promoting hope; problem solving; feedback; confidentiality and assessment of harm. The items are scored from 1 to 3, where 1 = needs improvement, 2 = partially done, 3 = done well and the final score ranges from 18 to 54. A score of at least 2 is required for all domains to achieve competence. A score of 43 represents a satisfactory level of competence and corresponds to 80 % of the total score. This tool can be used for role plays as described in the paper [24].

We will use ENACT in both control and intervention arms immediately after training and at 3 months. Independent outcome assessors, who are blinded to the training methodology used, will assess the LHWs on standardized patient role plays. These assessors will be trained by the THP trainers using the ENACT instrument, using role plays. Raters who performed the post-evaluation assessments will rate live observations of LHWs in the household settings using ENACT checklists after 3 months of training. We expect competency scores to increase as the LHWs gain more practice implementing the THP.

##### Qualitative evaluation – intervention feasibility

The qualitative evaluation will include exploring the views of health workers on training and supervision, acceptability of the content, and any challenges in implementation 3 months post training. Focus group discussions (FGDs) (*n* = 4) with LHWs and one FGD with LHSs will be conducted. Independent assessors having experience with qualitative data collection will conduct FGDs. They will be audio recorded and field notes will be taken. Data on LHW demographic variables, including age, experience, education, etc., will be collected.

#### Statistical analysis

The competence scores of the two groups will be compared using Student’s *t* test post training and at 3 months. A difference of less than 5 points between the two groups will be interpreted as supporting the non-inferiority hypothesis. We will also examine whether the competence scores improve at the 3-month mark after supervision. Stata software will be used for this. Qualitative data will be analyzed using framework analysis and manual software for qualitative studies. Cost-effectiveness will be assessed by combining costs with the primary outcome measure in incremental cost-effectiveness analysis. In addition, repeat re-sampling from the costs and effectiveness data (bootstrapping) will be used to calculate the probability that each of the training methods is the optimal choice, subject to a range of possible maximum values (ceiling ratio) that a decision-maker might be willing to pay for a unit improvement in ENACT score. A cost-effectiveness acceptability curve will be presented by plotting these probabilities for a range of possible values of the ceiling ratio [26].

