### Participant recruitment

The LHW program will be approached in the Swat district of Pakistan to obtain a list of the LHSs and LHWs who are currently working in the six LHS supervisory zones. Since Swat has extreme winter weather making some parts inaccessible in winters, the supervisory zones will be selected on the basis of accessibility throughout the year. The LHW program will be asked to inform all the LHSs and LHWs in the zones about the study. By simple random sampling 80 LHWs will be selected for the study and written informed consent will be obtained by the research team from the LHWs.

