### Sample size estimation

The primary outcome of the study is the mean competence scores post training and at 3 months. We define non-inferiority as a difference of 5 points or less (corresponding to a 10 % difference on the outcome measure score) in the mean competence score between the two groups. A sample size of 80 LHWs (40 LHWs per arm) will have 99 % power to detect a 5-point margin with a 0.05 one-sided alpha level. Even after potential attrition in this area, at 3 months we will need 30 health workers in each group for a power of 80 % and a two-sided alpha error of 0.05.

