### The intervention – TACTS

A tablet-based multimedia manual is developed for THP training and supervision purposes. The intervention material is divided into five training sessions, which are converted into narrative scripts by a panel of THP experts. The narratives have incorporated all the core techniques and principles of the intervention such as effective use of counseling skills, collaboration with the mothers’ families, guided discovery (style of questioning to probe mother’s health beliefs), and setting health-related tasks. Culturally appropriate real-life characters for the trainers and the trainees have been developed. An artist has converted the characters into “Avatars” (graphic image representing each character) (Fig. 1), which were used to voice the narrative scripts. Our group had successfully used this methodology of Technology-assisted Cascade Training (TACT) for training parents of children with developmental disorders [22]. The TACTS has also used case scenarios and role plays to reinforce key messages and training skills. For example, the role plays have demonstrated: sessions’ delivery by THP-trained LHWs to depressed mothers, dealing with challenging situations and dealing with adverse events. The training has been made interactive through suggesting activities for the actual trainees using a pause button and instructions. These activities are aimed to help them practice delivery of sessions through the role plays, peer assessment of role plays, reflecting on one’s learning, sharing relevant personal and work experiences, and practicing problem-solving strategies. A separate module on supervision has been developed for the LHSs to guide them on conducting supervisions. The software has the provision to modify and update the training scenarios. The software will be tested with LHSs and academics during and after the development process. The qualitative feedback regarding multiple aspects of the system and the user interface will be recorded.

In the intervention arm THP trainers (who have experience of delivering THP for 1 year) will give 5 days’ training to the LHS on THP-TACTS and will supervise three practice cases delivered by the LHSs. The LHSs will then cascade this training using THP-TACTS to train LHWs in 5-day training sessions (Fig 2).

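### The t test and the power statements treat all LHW scores as independent, although TACTS workers share LHS trainers and supervisors; any trainer effect specific to that arm makes the standard error too small

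*Protocol article*

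**What the plan says.** **Allocation and analysis.** The Randomization section allocates LHWs individually. Under Statistical analysis, "The competence scores of the two groups will be compared using" Student's t test at each of the two time points, with no term for trainer, supervisor or zone.

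**Delivery in the TACTS arm.** The intervention section says: "The LHSs will then cascade this training using THP-TACTS to train LHWs in 5-day training sessions". The Background adds that the LHSs supervise the LHWs as part of routine work. The Contamination section puts THP supervision in monthly group meetings.

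**Number of LHSs.** LHWs are drawn from those "currently working in the six LHS supervisory zones", and the Settings section describes one LHS per zone. Neither the number of LHSs who train, nor the class size, nor which LHS teaches whom is stated.

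**Control arm.** Specialists train the LHWs directly. The number of specialists and classes is not given.

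**Sample size.** "We define non-inferiority as a difference of 5 points or less". "A sample size of 80 LHWs (40 LHWs per arm) will have 99 % power to detect a 5-point margin", "with a 0.05 one-sided alpha level". After attrition, "we will need 30 health workers in each group for a power of 80 % and a two-sided alpha error of 0.05". No SD, ICC or design effect is given.

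**The concern.** Workers taught and then supervised by the same LHS share her skill as a THP trainer, so their ENACT scores are likely to be positively correlated. A t test on 80 scores assumes no such correlation. Individual randomization removes what both arms have in common, such as zone conditions. It does not remove an effect that acts only on the workers an LHS trains. The design is therefore partially nested.

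In a non-inferiority trial a standard error that is too small errs in the unsafe direction: it makes it easier to declare cascade training adequate when it is not. The trainer effect also belongs to the question. The stated purpose is scale-up through the LHW program, so variation between LHSs is part of the uncertainty in the claim. The stated power, especially the 80% figure for 3 months, would be optimistic for the same reason.

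**Working it through.** **Inputs from the article:** margin 5 points; 40 per arm at one-sided 0.05 with 99% power; 30 per arm at two-sided 0.05 with 80% power; six zones.

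**Assumptions:** six LHS trainers (one per zone), hence 40/6 = 6.67 or 30/6 = 5 TACTS workers per trainer; control scores independent; true difference zero for power; a trainer-specific ICC of 0.01 to 0.20, because the article gives none.

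**Step 1: the plan's own figures.** No SD is stated, so the power cannot be reproduced directly. Solving power = Φ(5/SE − z) with SE = SD·√(2/n):
- 99% at 40 per arm, one-sided 0.05: SD = 5/[(1.645 + 2.326)·√(2/40)] = 5.63.
- 80% at 30 per arm, two-sided 0.05: SD = 5/[(1.960 + 0.842)·√(2/30)] = 6.91.

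The two implied SDs differ. That is a separate matter; below, each power statement is given the SD that makes it true without clustering.

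**Step 2: effect of trainers in the TACTS arm only.**
- Design effect: DE = 1 + (m − 1)·ICC, with m workers per trainer.
- Correct SE = SD·√[(DE + 1)/n]; ratio to the t-test SE = √[(DE + 1)/2].
- Actual one-sided error of the unadjusted test = Φ(−1.645/ratio).
- Power with the correct SE = Φ(5/SE − z).

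Example at 40 per arm and ICC 0.10: DE = 1 + 5.67 × 0.10 = 1.57; ratio = √(2.57/2) = 1.13; error = Φ(−1.645/1.133) = 7.3%.

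| Trainer ICC | DE, 40/arm | SE ratio | One-sided error (nominal 5%) | Power, 40/arm (stated 99%) | DE, 30/arm | Power, 30/arm (stated 80%) |
|---|---|---|---|---|---|---|
| 0.01 | 1.06 | 1.01 | 5.2% | 98.8% | 1.04 | 79.2% |
| 0.05 | 1.28 | 1.07 | 6.2% | 98.1% | 1.20 | 76.2% |
| 0.10 | 1.57 | 1.13 | 7.3% | 96.9% | 1.40 | 72.5% |
| 0.20 | 2.13 | 1.25 | 9.4% | 93.7% | 1.80 | 65.8% |

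Simulation of the pooled t test against the margin at a true 5-point deficit gives 6.1–6.4%, 7.2–7.4% and 9.4–9.7% for ICC 0.05, 0.10 and 0.20, in line with the formula.

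**Step 3: few trainers.** With a t reference and Satterthwaite degrees of freedom, power for ICC 0.05, 0.10 and 0.20 is 97.1%, 95.2% and 90.6% at 40 per arm, and 70.5%, 66.0% and 58.2% at 30 per arm. Part of this drop comes from the degrees of freedom alone: at ICC 0 the same method gives 98.5% and 75.2%.

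**Step 4: shared zone effects.** The ICC above is the part specific to TACTS trainers. If half to three-quarters of a total within-LHS ICC of 0.10–0.20 is a zone effect common to both arms, simulated one-sided error is only about 5.1–7.0%, and somewhat higher if simple randomization splits the zones unevenly.

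**The case against.** Five points deserve weight.

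1. **The grouping is inferred.** A reader might infer that each LHS teaches her own class of six or seven. The article does not say so; several LHSs could jointly lead one or a few sessions, and the six-trainer calculation would then not fit the post-training score. This stands as a limit on the size. LHSs still train and supervise the arm, so the need to allow for it remains.

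2. **The t test is not tied to a margin test.** The analysis section says only that a difference below 5 points supports non-inferiority and mentions no confidence limit. Read literally, that is a rule on the point estimate, under which a true 5-point deficit passes about half the time, clustered or not. The error rates above therefore apply to a margin test or interval built on the t test, not to the literal wording.

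3. **Zone effects shared by both arms largely cancel.** A reader might treat all similarity among one LHS's workers as inflating the error. Randomization within common zones does not support that. The unadjusted t test also counts shared zone variance in its own standard error, which partly offsets the problem.

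4. **The planned sample is hardly underpowered.** A reader might infer that the 99% figure collapses. It stays at about 94% or more by normal approximation. The loss matters at 30 per arm, and there it depends on the SD of 6.91; with 5.63 the same formula gives 90.6%, 88.1% and 82.8%, from 93.0% unclustered.

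5. **The ICC is unknown.** Tablet-based material is meant to standardize the training, which argues for a small trainer effect.

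All five reduce the size or make it conditional. None makes independence the right assumption.

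**Conclusion.** The concern holds in a conditional form. The article documents that LHSs train and supervise the TACTS arm, and it fixes an analysis and power figures that assume independent scores. For any positive LHS effect specific to that arm, the standard error is too small and the power overstated.

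The size rests on six trainers, independent control scores and an assumed trainer-specific ICC. Over 0.05 to 0.20, one-sided error against the margin is about 6% to 9–10%. The loss of power is small at 40 per arm and material at 30 per arm, and larger once the small number of trainers enters the degrees of freedom. Fewer trainers, or clustering by specialist in the control arm as well, would make it worse. The documents do not support a claim that the design fails or that the planned 80 LHWs are too few.

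**What to change.** - Record for each LHW her LHS zone and the trainer or training group she actually had, and state the planned number of trainers and classes.
- Replace the t test by a linear model with arm and zone effects in both arms and a random trainer effect in the TACTS arm. Add a specialist or class effect in the control arm if there is more than one. Use Satterthwaite or Kenward-Roger degrees of freedom. The zone term spanning both arms keeps shared zone variance from being attributed to trainers.
- Compare the confidence limit from that model with the 5-point margin.
- Restate the sample size paragraph's power over a range of trainer ICC, with the assumed SD given.
- In the cost-effectiveness bootstrap, resample whole TACTS trainer groups.

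The cost is revised analysis wording, two identifiers per LHW, a somewhat wider interval and a less favourable stated power. No additional LHWs are needed. The Trial status section reports that enrollment has not begun, so the change can be prespecified.

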### Settings

We intend conducting the study in the Swat district in Northern Pakistan which has been affected by multiple humanitarian crises in recent years. Swat has a population of 1,257,602 persons, 86 % of whom live in rural areas with the average household size of 8.8 persons with a low female literacy. The resurgence of the Taliban movement in the Swat Valley of Pakistan since 2004, and the military operations in 2009 and the displacement of residents has created a humanitarian crisis in the area [19]. The devastating floods of 2010 led to thousands of people losing of their homes, and caused destruction to houses, roads, schools and health facilities [20, 21]. A recent community-based cross-sectional survey of 349 pregnant women in Swat showed that the prevalence of current psychological distress was 38.1 % [22]. Mental health impacts of conflict are often severe [8, 23] and may not be depicted in the national statistics. The health infrastructure of a post-conflict zone like Swat is particularly fragile with the health workers under threat of being attacked, thus compromising their training and supervision. The district has a functioning LHW program and LHWs, who have 10–14 years of education and provide preventive primary care services in the community, have the capacity to use technology. A Lady Health Supervisor (LHS) supervises 15–20 LHWs in one supervisory zone.

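### The 3-month ENACT comparison is a stand-alone t test that ignores the post-training scores of LHWs lost by then; one joint model would use them, for a modest gain

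*Protocol article*

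**What the plan says.** All references are to the protocol article.

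- **Statistical analysis:** "The competence scores of the two groups will be compared using" Student's t test at each of the two time points. No covariate is named, and no model links the two occasions.
- **Sample size estimation:** The primary outcome is mean competence at both time points. "We define non-inferiority as a difference of 5 points or less". At full size, "A sample size of 80 LHWs (40 LHWs per arm) will have 99 % power" "to detect a 5-point margin with a 0.05 one-sided alpha level". After attrition, "at 3 months we will need 30 health workers in each group" "for a power of 80 % and a two-sided alpha error of 0.05". No SD is given.
- **Outcome measure:** ENACT is scheduled in both arms directly after training, on standardised role plays, and again at 3 months, on live household observation. No pre-training ENACT is scheduled there.
- **Qualitative evaluation:** "Data on LHW demographic variables, including age, experience, education, etc., will be collected". The timing is not stated, nor whether all 80 LHWs are covered.
- **Settings:** LHWs "have 10–14 years of education and provide preventive primary care services in the community".
- **Cost evaluation:** Regression adjustment is planned for costs. None is mentioned for ENACT.

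**The concern.** A non-inferiority conclusion depends on how far the interval for the arm difference stays from the margin, so both the width and the centre of that interval matter. A separate t test at 3 months is a complete-case analysis. An LHW who was scored after training and then lost contributes nothing to it, although her first score carries information about what her second would have been.

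Two things follow if attrition is near the level the article allows for. The interval is somewhat wider than the scheduled data permit. And if loss depends on post-training competence, and does so differently in the two arms, the 3-month difference among those who remain is a biased estimate of the difference among those randomised. In this design the bias could run in either direction, including towards non-inferiority.

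**Working it through.** **1. The plan's own power figures.** The SD has to be solved from them, because none is stated. With a true difference of 0 and a margin of 5, the normal approximation gives SD = 5 / (√(2/n) × (z_alpha + z_power)).

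- 40 per arm, one-sided 0.05, 99%: 5 / (0.2236 × (1.645 + 2.326)) = 5.63. The noncentral t gives 5.58.
- 30 per arm, two-sided 0.05, 80%: 5 / (0.2582 × (1.960 + 0.842)) = 6.91. The noncentral t gives 6.80.

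No single SD yields both statements. Results are therefore shown for SD 5.6 and SD 6.8, with noncentral-t power at 30 per arm and two-sided 0.05.

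**2. Gain from a joint model.** Assume 40 per arm scored after training, 30 of them scored again at 3 months, and correlation r between the two scores. The large-sample variance of the 3-month difference, relative to the t test, is

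1 − r² × (1 − 30/40) = 1 − 0.25 r².

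The t-test standard error is SD × √(2/30), which is 1.756 for SD 6.8 and 1.446 for SD 5.6.

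| r (assumed) | Variance factor | SE, SD 6.8 | Power, SD 6.8 | SE, SD 5.6 | Power, SD 5.6 |
|---|---|---|---|---|---|
| t test | 1 | 1.756 | 80.0% | 1.446 | 92.5% |
| 0.3 | 0.978 | 1.736 | 80.9% | 1.430 | 93.0% |
| 0.5 | 0.938 | 1.700 | 82.4% | 1.400 | 94.0% |
| 0.7 | 0.878 | 1.645 | 84.8% | 1.354 | 95.3% |

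If nobody is lost, the factor is 1 and the model with arm-by-time effects returns the same 3-month difference as the t test.

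**3. Bias.** Let b be the slope of the 3-month score on the post-training score. Suppose loss depends only on the post-training score, and the LHWs who remain in an arm average s points above that arm's full post-training mean. The complete-case 3-month mean in that arm is then off by b × s, and the arm difference by b × (s_TACTS − s_specialist). This vanishes if the selection is the same in both arms. The joint model corrects it under that missing-at-random assumption; the t test does not.

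**4. Why the post-training score cannot be a covariate.** It is measured after randomisation and is itself part of the primary outcome. Conditioning on it estimates D3 − b × D0, where D0 and D3 are the arm differences after training and at 3 months. With D3 = −6 (outside the margin), D0 = −5 and b = 0.5, the result is −6 + 2.5 = −3.5, which is inside the margin.

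**5. Optional adjustment for age, education and experience.** With three covariates and 60 LHWs, the residual variance falls by the factor 1 − R². Chance imbalance inflates the variance by about 1 + 3/54 = 1.056, and three degrees of freedom are lost. R² is assumed.

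| R² | Variance factor | Power, SD 6.8 | Power, SD 5.6 |
|---|---|---|---|
| no adjustment | 1 | 80.0% | 92.5% |
| 0 | 1.056 | 77.7% | 91.1% |
| 0.05 | 1.003 | 79.8% | 92.4% |
| 0.10 | 0.950 | 81.9% | 93.6% |
| 0.20 | 0.844 | 86.1% | 95.9% |

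**The case against.** The strongest reply is that nothing here is wrong. LHWs are individually randomised, the unadjusted t test is valid, and its standard error already reflects chance imbalance. Repeated-measures models and covariate lists are often left to an analysis plan, and none is shown. This stands in so far as the point is not an error. It does not remove the point, because the article does name a test for each time point, and a better use of the scheduled scores is available.

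The gain may also be at the low end. The two occasions differ in setting (role play, then household observation), and nothing in the article supports a correlation of 0.5 or more. At 0.3 the gain is about one power point. That stands too.

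A reader might infer more than the documents support:

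- **That the trial throws away substantial free precision by not adjusting for demographics.** The article does not say that these data are collected for all 80 LHWs, or that they predict ENACT. Three covariates gain nothing at R² 0.05 and lose about 2 points at R² 0 (SD 6.8).
- **That every LHW will have a post-training score.** The assessment is scheduled for both arms; completeness is not assured.
- **That 3 months is planned at only 80% power.** Thirty per arm is the number needed after possible attrition, not the number recruited, and the statement uses two-sided 0.05. At one-sided 0.05 the same 30 per arm with SD 6.8 gives about 88%.

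**Conclusion.** The point holds as a low-cost improvement. Separate t tests leave the post-training scores of lost LHWs out of the 3-month comparison; a joint model would use them.

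The precision gain is modest, about 1 to 5 power points with SD 6.8 and about 0.5 to 3 with SD 5.6. It rests on assumed correlations of 0.3 to 0.7, an SD solved from two power statements that do not agree, and attrition of 10 in 40 per arm. With less attrition the gain shrinks towards nothing. The protection against complete-case bias may matter more, but its size cannot be given from the documents, and it depends on loss being explained by the post-training score.

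The documents do not support calling the t test invalid, or claiming a sizeable gain from demographic adjustment.

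**What to change.** 1. In Statistical analysis, make the primary estimate at both time points come from one repeated-measures model with arm, time and arm-by-time effects and an unstructured covariance, fitted to every LHW with at least one ENACT score. Report the TACTS-minus-specialist difference and its interval at each time point, and compare the interval with the 5-point margin.
2. State that the post-training score enters only as an outcome, not as a covariate.
3. Keep the two t tests as sensitivity analyses.
4. Optionally, prespecify one or a few prognostic covariates, for example years of education and of experience, recorded for all 80 LHWs at enrolment. Keep the list short, since weak covariates cost power at this sample size.

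Items 1 to 3 cost only analysis wording; the scores are already scheduled and Stata is already the named software. Item 4 needs a short form or programme records, and a degree of freedom per covariate. The article says enrolment has not started, so all of this can be fixed before any data are seen. The differing alpha levels and implied SDs in Sample size estimation are a separate matter, but the level of the interval in item 1 depends on settling them.

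### Non-inferiority is concluded from the size of the mean difference alone, so as written a TACTS arm truly 5 points worse passes about half the time at each time point

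*Protocol article*

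**What the plan says.** The protocol article states the criterion in three places, each time as the size of a difference in mean competence score:

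- **Sample size estimation:** "We define non-inferiority as a difference of 5 points or less (corresponding to a 10 % difference on the outcome measure score").
- **Primary outcome – competence of health workers:** "Equivalence is defined as a difference of less than 5 points (10 %) in the mean score of the competence measure across the two groups".
- **Statistical analysis:** "The competence scores of the two groups will be compared using Student’s *t* test post training and at 3 months", followed by "A difference of less than 5 points between the two groups will be interpreted as supporting the non-inferiority hypothesis".

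The error rates appear only under Sample size estimation. The main statement is "A sample size of 80 LHWs (40 LHWs per arm) will have 99 % power to detect a 5-point margin with a 0.05 one-sided alpha level". The next sentence, on attrition, gives 30 per group, 80% power and a two-sided alpha of 0.05. Neither alpha is linked to the decision rule. No section applies a confidence limit, or a test against the 5-point margin, to the competence score.

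**The concern.** A non-inferiority claim needs evidence that the true deficit is smaller than the margin. That means comparing a confidence limit with the margin, or equivalently testing a null hypothesis placed at the margin. The stated rule compares a difference between groups with 5 and says nothing about its uncertainty. An imprecise estimate just under 5 then counts the same as a precise one near 0, and the alpha used to size the trial does not govern the conclusion.

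The t test does not repair this as described, because its null value is not given and its result is not tied to the conclusion. The direction is also left loose: no sign is attached to the difference, and one section names the criterion equivalence although the design is non-inferiority.

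At stake is the primary objective. The claim that technology-assisted training matches specialist training is what would support scale-up, and it would rest on a rule with no controlled false-positive rate.

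**Working it through.** **Inputs from the protocol article.** Margin 5 points; 40 per arm, 99% power, one-sided alpha 0.05; 30 per arm, 80% power, two-sided alpha 0.05; two assessments (post training and 3 months). No SD is given.

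**1. The plan's own power figures.** These cannot be reproduced without an SD, so I solved for it, taking a true difference of zero. The normal approximation is SD = 5 / [√(2/n) × (z for alpha + z for power)].

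- 40 per arm, one-sided 0.05, 99%: 5 / [0.2236 × (1.645 + 2.326)] = 5.63; with the noncentral t, 5.58.
- 30 per arm, two-sided 0.05, 80%: 5 / [0.2582 × (1.960 + 0.842)] = 6.91; with the noncentral t, 6.80.

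The two statements imply different SDs. Steps 2 and 3 do not depend on either value.

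**2. Error rate of the stated rule at one time point.** Let D be the observed deficit (specialist minus TACTS) and let the true deficit be 5. D is symmetric about 5, so P(D < 5) = Φ[(5 − 5)/SE] = Φ(0) = 0.50 for any SE. A simulation of 100,000 trials gave 0.499 with SD 5.63 and 40 per arm, and again with SD 6.91 and 30 per arm. Reading the rule as an absolute difference below 5 gives 0.499 to 0.500 for SDs from 4 to 12.

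**3. Two time points.** With a true deficit of 5 at both and correlation ρ between the two estimates, P(both pass) = 1/4 + arcsin(ρ)/(2π) and P(either passes) = 3/4 − arcsin(ρ)/(2π).

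| ρ | both | either |
|---|---|---|
| 0 | 0.25 | 0.75 |
| 0.3 | 0.30 | 0.70 |
| 0.5 | 0.33 | 0.67 |
| 0.8 | 0.40 | 0.60 |

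**4. What a confidence-limit rule would require (illustration only, using the back-solved SDs).** SE = SD × √(2/n).

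- SD 5.58, 40 per arm: SE = 1.25; largest passing deficit with a one-sided 95% limit = 5 − 1.665 × 1.248 = 2.9 points.
- SD 6.80, 30 per arm: SE = 1.76; largest passing deficit = 5 − 1.672 × 1.756 = 2.1 points.

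**5. Error rate after the change.** In the same simulations, requiring the one-sided 95% limit to exclude a 5-point deficit gave a false-pass rate of 4.9% (SD 5.63, 40 per arm) and 4.8% (SD 6.91, 30 per arm). A 97.5% limit gave about 2.4% in both.

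**The case against.** The strongest reply is that the sentence is shorthand. The article condenses a fuller plan, says that CONSORT will be followed, and gives a margin and a one-sided alpha in one paragraph. The word observed does not appear in the rule. The authors may have intended inference against the margin at that alpha. That is possible, but this is not a detail left to an analysis plan. The article states the rule, words the criterion as a difference in means in all three places, and nowhere links it to an alpha. An analysis plan that used a confidence limit would depart from the published rule.

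A second reply is that a non-significant t test might be required as well. The article does not say so. If it were, with 40 per arm the false-pass rate at a true 5-point deficit would be about 2% at SD 5.63, 10% at SD 6.91 and 50% at SD 12. The error would still be uncontrolled, and noisier data would make success easier.

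Some stronger readings that a reader might infer are not supported:

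- *The t test necessarily tests a zero difference.* The article states no null. A Student's t test can be run against a 5-point shift and yields the interval needed. The fair criticism is that the null is unspecified.
- *The plan contradicts itself, because a deficit could be significantly worse than zero yet non-inferior.* That is an ordinary outcome of a valid non-inferiority analysis. The corrected rule allows it too: with SD 5.58 and 40 per arm, at deficits of about 2.5 to 2.9 points.
- *A TACTS arm 6 points better would fail, or an equivalence reading leaves the trial underpowered.* The design, the analysis sentence and the one-sided alpha all point to non-inferiority, so the equivalence label is a real but minor inconsistency. Low power would follow only from a formal two-sided equivalence test, which the article does not describe. The literal rule, as an absolute difference below 5, would pass a true 3-point advantage about 87-95% of the time: Φ(2/1.76) to Φ(2/1.25), the other tail being negligible.

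**Conclusion.** The concern holds, and the rule should be corrected before the trial is analysed. As written it does not control the false-positive rate of the primary claim: about 50% per time point at a true 5-point deficit, against a nominal 5% (or 2.5% under the two-sided alternative).

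The 50% rests only on the literal reading of the rule and a symmetric sampling distribution. It needs no SD and no sample size. It is the error rate at the margin, not the chance that this trial reaches a wrong conclusion, and it falls as the true deficit grows beyond 5. The overall figure across the two assessments depends on how they combine, which the article does not say, but every version considered is far above the nominal rate. The thresholds of 2.9 and 2.1 points are illustrations, because they rest on SDs that the article does not state.

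**What to change.** Use one directional rule in Sample size estimation, Primary outcome and Statistical analysis, for example: *Non-inferiority is concluded if the lower confidence limit for the mean ENACT difference (TACTS minus specialist) lies above -5 points.* With it:

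- choose a single alpha from the two in the sample size section and match the interval to it: a one-sided 95% limit for one-sided 0.05, or a two-sided 95% interval if two-sided 0.05 is kept;
- say whether one named time point or both must pass;
- replace the equivalence definition under Primary outcome with this one-sided rule.

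The article reports that enrollment has not started, so the change is to wording only. Its cost is a harder test: the observed deficit must be clearly below 5 points, by an amount set by the SD and the number assessed. The stated power may already assume such a test, but this cannot be confirmed because the sample size section shows neither an SD nor a formula.
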